## Abstract

**Background:**

Core stability exercise (CSE) is a globally acknowledged intervention for managing chronic low back pain. However, the sustained adherence of patients with chronic low back pain to CSE can be challenging, mainly due to the absence of supervision and guidance from physical therapists during home-based exercise sessions. Consequently, exercise compliance tends to decline, resulting in suboptimal long-term effectiveness of the intervention. In this trial, our primary aim is to evaluate the potential therapeutic equivalence between home-based rehabilitation training employing key point identification technology and exercise guidance administered in a hospital setting.

**Methods:**

In this trial, we will randomly assign 104 adults with chronic low back pain (CLBP) to either an intervention or control group, with 52 participants in each group. Both interventions will consist of three weekly 0.5-h sessions of core stability exercise (CSE). The intervention group will engage in home rehabilitation training utilizing key identification technology for movement, while the control group will perform supervised exercises in a hospital setting. Outcome assessments will be conducted at 4 weeks and 16 weeks after randomization. The primary outcome measure will be the change in pain intensity based on numeric rating scale (NRS scores) from baseline to 4 weeks. Secondary outcomes will include changes in physical function (measured by the Oswestry Disability Index (ODI)) and lumbar spine mobility as well as activity participation and treatment satisfaction.

**Discussion:**

If home-based rehabilitation method is demonstrated to be non-inferior or even superior to traditional face-to-face exercise guidance, it could significantly advance the adoption of digital medical care and contribute to improving the overall health of the population.

**Trial registration:**

NCT05998434. Registered on 16 August 2023.

## Introduction

### Background and rationale {6a}

Low back pain (LBP) is a significant global public health issue that affects populations across different regions and age groups [1]. Nonspecific chronic low back pain (NCLBP), also referred to as chronic low back pain (CLBP), is characterized by low back pain lasting for more than 3 months without identifiable pathological anatomical factors [2]. The global burden of low back pain is substantial, with an estimated 568.4 million cases reported in 2019, equating to 6972.5 cases per 100,000 individuals [3]. The incidence of low back pain is increasing, and it is projected that by 2050, approximately 843 million individuals worldwide will be affected by this condition due to population growth and aging [4]. With the popularity of smartphones and computers, prolonged sitting and poor posture, such as forward head posture, have become prevalent behaviors among the majority of people [5]. The incidence of spinal pain, particularly neck and lower back pain, continues to increase, leading to an increased rate of sick leave and imposing significant medical and economic burdens on society [6]. In China, the prevalence of chronic pain is reported to be 31.54%, with low back pain being the most prevalent condition at 74.1% [7].

Core stability exercise (CSE) has demonstrated effectiveness in treating chronic low back pain [8–10]. However, frequent visits to the hospital for therapy impose significant time and financial burdens on patients [11]. Traditional home rehabilitation training, lacking supervision and guidance from therapists, often results in suboptimal long-term efficacy of exercise therapy [12]. Therefore, it is essential to develop a convenient and reliable intelligent spinal health AI management system that integrates risk prediction, diagnosis, assessment, treatment, and rehabilitation.

Tele-rehabilitation technology based on mobile health (m-health) has experienced rapid development, especially during the COVID-19 outbreak [13]. This technology enables patients to receive exercise instructions through mobile devices and engage in rehabilitation treatment anytime and anywhere [14]. Our preliminary exploratory study has indicated that core stability training instruction provided remotely has the potential to improve lower back function and reduce pain intensity in patients with chronic low back pain [15]. Research has demonstrated that remote education and exercise guidance via videoconferencing hold promise in achieving therapeutic effects [16]. However, these interventions have not provided patients with objective and accurate supervision and exercise guidance in their homes. Research has shown that unsupervised app-based treatments have not demonstrated significant treatment efficacy and cost-effectiveness [17].

Digital exercise-based interventions have shown great potential in the management of musculoskeletal conditions [18]. The study conducted by Thoma et al. demonstrated the effectiveness of the Kaia application as a multidisciplinary back pain intervention, surpassing a combination of physical therapy and online education, for patients with low back pain [19]. However, it remains unclear whether AI-based intelligent home rehabilitation training will yield comparable therapeutic effects to exercise treatment in a hospital setting. In this study, we will employ human key point detection technology to monitor patients in real time during home rehabilitation training. We will record the duration of patients’ training sessions and assess the quality of their movements, comparing these results with those of traditional on-site exercise guidance.

### Objectives {7}

The objective is as follows: to assess the comparable therapeutic effects of home rehabilitation training using human key point detection technology compared to exercise instruction in a hospital setting.

### Trial design {8}

We are planning to conduct a randomized controlled non-inferiority clinical trial. Eligible participants will be randomly allocated in a 1:1 ratio into either the experimental group or the control group. The experimental group will undergo home rehabilitation training with guidance from human key point detection technology, whereas the control group will receive exercise instruction in a hospital setting. The trial protocol will adhere to the Standard Protocol Items: Recommendations for Interventional Trials (SPIRIT 2013) guidelines for conducting and reporting clinical trials [20].

### Experiment duration

The intervention spanned a total of 4 weeks, with participants engaging in 30-min training sessions three times a week. Clinical follow-up assessments were scheduled at week 4 and week 16. The research project is scheduled to take place from January 2024 to December 2025. The experimental flowchart is shown in the figure (Fig. 1).

**Fig. 1 Fig1:**
[figure not shown]
Flow chart

## Methods: participants, interventions and outcomes

### Study setting {9}

The RCT is being undertaken in China. The study site is located in the outpatient Department of Rehabilitation of the First Affiliated Hospital of Sun Yat-sen University, and participants in Guangzhou will be mainly recruited for the study.

### Eligibility criteria {10}

Inclusion criteria(1) Age between 18 and 60 years.(2) Duration of low back pain of at least 12 weeks.(3) Strong willingness to participate in the study and signed informed consent.

Exclusion criteria(1) Presence of potential “red flag signs” (e.g., unilateral leg pain and numbness consistent with nerve distribution, intermittent claudication, unexplained sudden weight loss, nocturnal lumbar pain, traumatic lumbago).(2) NRS score less than 4 points.(3) Regular engagement in core stability training in the past 4 weeks.(4) Inability to independently complete the Chinese electronic questionnaire.

Exit criteria(1) Withdrawal due to sudden personal reasons.(2) Withdrawal due to apparent loss of interest in participation.(3) Failure to complete the prescribed treatment tasks as required and requesting withdrawal due to unexcused absence.

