### Control group

The participants randomly assigned to the control group will receive traditional face-to-face exercise instruction. An experienced therapist (10 years of experience) will be arranged to provide the subjects with 20–30 min of exercise instruction three times a week for 4 weeks [24]. The training sessions were scheduled to start at 4 p.m. on Monday, Wednesday, and Friday of each week. The exercise training content selected for the control group will be consistent with that of the intervention group.

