### Criteria for discontinuing or modifying allocated interventions {11b}

*Medical safety concerns*: If a participant experiences any adverse events or medical complications that are directly related to the allocated exercise program, discontinuation or modification should be considered. This could include issues like musculoskeletal injuries, cardiovascular symptoms, or other medical conditions exacerbated by exercise.*Non-adherence*: If a participant consistently fails to adhere to the prescribed exercise regimen, it might be necessary to modify the program to better suit their schedule, preferences, or physical capabilities. Non-adherence can affect the efficacy of the intervention and overall study outcomes.*Technology issues*: Given the remote nature of the intervention, technical issues may arise that hinder the participant’s ability to engage effectively. In such cases, modifications to the technology setup or the exercise routine may be required.

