## Statistical methods

### Statistical methods for primary and secondary outcomes {20a}

Statistical analysis was conducted according to intention-to-treat (ITT). The chi-square test was used to analyze categorical variables when comparing baseline demographic and clinical characteristics; For continuous variables, we first performed exploratory data analysis and Shapiro–Wilk tests to determine the normality of our data distribution, using independent *t* tests when the results conform to a normal curve and non-parametric rank sum tests when they do not.

To analyze the data, we will employ repeated measures analysis of variance (RM-ANOVA) as the statistical method. Our primary interest lies in comparing the changes over time between the intervention and control groups at baseline, 4 weeks, and 16 weeks. We will utilize repeated measures ANOVA to examine the main effects between the two groups while considering the factors of time and group. As part of the analysis, multiple comparisons will be performed, including comparisons between baseline and 4 weeks, baseline and 16 weeks, and 4 weeks and 16 weeks. These comparisons will help identify significant differences across different time points. To assess statistical significance, appropriate statistical indicators such as *F*-values and *p*-values will be utilized. In case of significant differences, post hoc multiple comparison analyses will be conducted to determine specific time points of significance. Finally, descriptive statistics and appropriate graphical representations will be employed to illustrate the overall trends and changes in the data. Statistical analyses were done using the SPSS software for Windows, version 23.

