### Methods in analysis to handle protocol non-adherence and any statistical methods to handle missing data {20c}

For continuous outcomes, such as numeric rating scale (NRS) scores, a multiple imputation approach will be utilized to address missing data. Imputation will be performed using covariates and auxiliary variables that are pertinent to the analysis. The imputed datasets will be subject to analysis, and the outcomes will be aggregated to ensure unbiased estimations and reliable inferences. To enhance the robustness of findings in the presence of missing data, sensitivity analyses will be conducted. These analyses will evaluate the resilience of results to diverse assumptions concerning missing data. Variation in imputation methodologies or mechanisms will be explored to assess their potential impact on the derived conclusions. By incorporating sensitivity analyses, the credibility of outcomes will be fortified across a spectrum of scenarios.

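### Exit rules tied to non-adherence, with ITT and imputation alone, can lose the outcomes of those who stop training and bias the non-inferiority comparison in either direction

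*Protocol article*

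**What the plan says.** All references are to the protocol article.

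- **Exit.** Eligibility criteria {10} lists three exit criteria: withdrawal for sudden personal reasons, withdrawal for apparent loss of interest, and "Failure to complete the prescribed treatment tasks as required and requesting withdrawal due to unexcused absence".
- **Non-adherence.** Section {11b} treats it differently: "If a participant consistently fails to adhere to the prescribed exercise regimen, it might be necessary to modify the program". Exit is not mentioned there.
- **Design.** Trial design {8}: "We are planning to conduct a randomized controlled non-inferiority clinical trial".
- **Analysis set.** Section {20a}: "Statistical analysis was conducted according to intention-to-treat (ITT". No other set is named.
- **Missing data.** Section {20c} is headed as covering protocol non-adherence as well as missing data, but its text deals only with missing data. For continuous outcomes such as the NRS, "a multiple imputation approach will be utilized to address missing data". On the model it says: "Imputation will be performed using covariates and auxiliary variables that are pertinent to the analysis". It adds sensitivity analyses under other missing-data assumptions without specifying them.
- **Adherence records.** The secondary outcomes section provides for control-arm sign-in and for mini-program logging of home-arm frequency and quality.
- **Control schedule.** "The training sessions were scheduled to start at 4 p.m. on Monday, Wednesday, and Friday of each week".

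Nothing states whether someone who exits still receives the week-4 and week-16 questionnaires.

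**The concern.** The trial's premise is that home exercise fails when people stop doing it. Participants who lose interest or stop completing sessions therefore carry much of the answer. If leaving training also means leaving data collection, their pain scores are never observed. An analysis labelled ITT then rests on a model for them, and unless that model uses adherence it treats those who stopped as similar to those who stayed.

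With 20% dropout planned and a margin of one NRS point, that substitution could move the estimate by a material part of the margin. A later analysis plan cannot recover outcomes that were not collected.

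A second, separate gap is that no adherence-based analysis is named. In a non-inferiority trial, poor adherence among participants who are retained, especially in the comparator, can pull the arms together, and ITT alone gives no check on that.

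**Working it through.** **Inputs from Sample size {14} and the Abstract.** Pilot NRS decrease 1.6 (SD 2.0) in the home arm and 1.9 (SD 1.9) in the control arm; margin 1; alpha 0.05, sidedness not stated; power 0.9; dropout 20%, not split by arm or reason; 52 per group.

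**The plan's own figure.** n = 2 × SD² × (z₀.₉₅ + z₀.₉₀)² / distance² = 2 × 4 × (1.645 + 1.282)² / 1.3² = 40.5, so 41 per group. Then 41 / 0.8 = 51.25, so 52 per group and 104 in all. The 41 reproduces with one-sided alpha 0.05, which is used below. It also needs the 0.3 to be added to the margin, although the pilot has the home arm worse. That is a separate matter and nothing here depends on it.

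**Assumptions not in the documents.** Exits average 20% but split differently between arms. Exiters improve by D points less than those who stay, with the same D in both arms, from 0.5 to 1.9 (1.6 and 1.9 equal the loss of a whole pilot improvement). Exiters are not followed. Imputation ignores adherence, so its estimate is approximated by that of completers.

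**Bias** in the home-minus-control difference in NRS decrease (positive favours home) = D × (home exit rate − control exit rate).

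**False non-inferiority** when the true difference among all randomised is exactly −1: Φ(bias/SE − 1.645), with SE = √(2.0²/n_home + 1.9²/n_control) and n the expected completers out of 52.

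Example for 30%/10%, D = 1.6: bias = 1.6 × 0.20 = 0.32; SE = √(4/36.4 + 3.61/46.8) = 0.432; Φ(0.74 − 1.645) = 0.18.

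| Exits home/control | Bias, D = 0.5 to 1.9 | Formula, D = 1.6 | Simulation, D = 1.6 |
|---|---|---|---|
| 30%/10% | +0.10 to +0.38 | 18.3% | 18.1% |
| 25%/15% | +0.05 to +0.19 | 10.2% | 10.7% |
| 20%/20% | 0 | 5.0% | 5.4% |
| 15%/25% | −0.05 to −0.19 | 2.2% | 2.6% |
| 10%/30% | −0.10 to −0.38 | 0.8% | 0.8% |

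The simulation used 5,000 trials per row. The two extremes of bias, ±0.38, need D = 1.9. At that D the 30%/10% formula gives Φ(0.38/0.432 − 1.645), about 22%.

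**Equal exits, unequal shortfalls.** If 20% exit in each arm and each exiter loses the whole pilot improvement of that arm, bias = 0.2 × 1.6 − 0.2 × 1.9 = −0.06, slightly against non-inferiority.

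**With exiters followed and analysed**, simulated false non-inferiority is 4.7% to 5.4% in all five patterns.

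**The case against.** The strongest case on the other side has four parts.

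1. *Missed training does not by itself remove anyone.* Criterion 3 joins it to a request to withdraw, the other two criteria are worded as withdrawals, and section {11b} provides for modification. This stands: the text is ambiguous, and a reader who infers that non-adherent participants are automatically exited goes beyond it. It does not settle what happens to the outcomes of those who do exit.
2. *The article does not say that scores are imputed from adherent completers.* Section {20c} names no donor set, adherence is recorded in both arms and could be in the model, and sensitivity analyses are planned. This also stands. The bias above is conditional on adherence being left out of the model.
3. *A reader might infer that the plan favours a non-inferiority finding, with an error rate near 18%.* The documents do not support that direction. The figure needs an excess of uncompensated losses in the home arm. Optimistic imputation in the control arm makes the comparator look better, which works against non-inferiority. The fixed 4 p.m. hospital sessions, and the time and cost of hospital visits cited in the Background, make more control-arm exits plausible. For the control arm, the two mechanisms also oppose each other: dilution needs poor adherers' outcomes to stay in the analysis, while imputation replaces them.
4. *Analysis sets and imputation variables are commonly left to an analysis plan, and a per-protocol set conditions on behaviour after randomisation.* This is fair. It is why the per-protocol analysis should be supportive only, and why agreement with ITT should not be a condition for claiming non-inferiority. It does not cover follow-up after exit, which governs what data are collected, or the conflict between sections {10} and {11b}.

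**Conclusion.** The point holds as a risk of bias whose direction the documents do not fix. Sections {10} and {11b} handle non-adherence differently and must be reconciled. Outcome collection after exit is unstated. Section {20c} announces non-adherence in its heading but gives no adherence-based analysis.

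Under the assumed splits the bias runs from about −0.38 to +0.38 NRS points, up to 38% of the margin. False non-inferiority runs from about 1% to 18% against a nominal 5% when the shortfall is 1.6. The bias is zero with equal exits and equal shortfalls, and about −0.06 with equal exits and full loss of each arm's pilot benefit.

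These sizes rest on the assumed exit splits and shortfalls, on no follow-up after exit, on an imputation model without adherence, and on one-sided alpha 0.05. The change is worth making because following exiters holds the error rate near 5% whichever arm loses more. It should be made before recruitment, which Trial status places in January 2025.

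**What to change.** 1. Reconcile the exit criteria in {10} with {11b}. Whichever rule on training is kept, state that exit ends training only, and that the week-4 and week-16 electronic questionnaires still go to every randomised participant unless consent to data collection is withdrawn.
2. In {20c}, add a supportive per-protocol analysis with one session-count threshold common to both arms, taken from the sign-in and mini-program records already planned. Report it beside ITT.
3. In {20c}, name recorded adherence as a variable in the imputation model. Fix one delta-adjusted sensitivity analysis: worsen imputed scores in steps up to the 1.0 margin, vary the penalty by arm, and report the step at which the conclusion changes.

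**Cost.** Protocol wording and a little more analysis. The questionnaires are already electronic and attendance is already logged, so these changes add no visits. The downside is that a non-inferiority claim may look less robust if the analyses disagree.

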### Who will take informed consent? {26a}

A study researcher ([name]) will introduce the trial to potential participants and discuss the trial with them. If the patient agrees, the researcher will obtain a written consent form stating that the patients are willing to participate in the trial.

### Additional consent provisions for collection and use of participant data and biological specimens {26b}

Not applicable, as this study primarily assessed efficacy using subjective scales. This trial does not involve collecting biological specimens for storage.

#### Interventions

### Explanation for the choice of comparators {6b}

Face-to-face core stability training guidance is a traditional and proven treatment method. However, it may not be feasible for individuals residing in remote areas or with busy schedules. To verify the effectiveness of home-based rehabilitation, we selected traditional face-to-face exercise guidance as the control group.

#### Intervention description {11a}

### Intervention group

The participants randomly assigned to the intervention group will receive home-based exercise training with human key point detection. They will be instructed to complete a minimum of three sports training sessions per week at their preferred time and location. The exercise prescription will be formulated based on previous comprehensive studies [21–23], encompassing exercises targeting strength, balance, flexibility, and mobility. Human key point detection technology accurately estimates 25 key points of the human body in pictures or videos using visual detection. These key points include the left and right elbow, left and right wrist, left and right shoulder, head, neck, left and right ankle, left and right knee, and left and right hip, among others. The technology allows for accurate estimation of standing, sitting, and moving postures in various scenes, facilitating the detection and recognition of action postures. Yinshan Future Health Technology (Beijing) independently developed this human body key point detection technology, which includes self-assessment and intelligent rehabilitation training. Participants receive treatment and evaluation through the WeChat mini-program. For autonomous assessment, participants can report their medical history and independently measure their spinal range of motion following the provided prompts. The data is automatically stored for therapists and physicians to review (see Fig. 2 for a specific demonstration).

**Fig. 2 Fig2:**
[figure not shown]
Example of Yinshan mini program

### Control group

The participants randomly assigned to the control group will receive traditional face-to-face exercise instruction. An experienced therapist (10 years of experience) will be arranged to provide the subjects with 20–30 min of exercise instruction three times a week for 4 weeks [24]. The training sessions were scheduled to start at 4 p.m. on Monday, Wednesday, and Friday of each week. The exercise training content selected for the control group will be consistent with that of the intervention group.

